### Sample size

The sample size calculation is based on the primary outcome of 28 days of mortality in patients with sepsis. It was estimated that the sepsis mortality rate within 28 days would be 40%. We used the superiority test for two proportions based on the one-sided 2.5% of type I error probability and 80% of power. A total of 620 participants are required to detect a decrease of 10% mortality rate and 10% dropout rate. The sample size was calculated by PASS 15 software (NCSS, Kaysville, UT, United States).

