### Randomization, Blinding, and allocation

Participants are randomly assigned to the vitamin C or normal saline (NS) groups in a 1:1 ratio. The randomization sequence is generated with SAS v. 9.2 (SAS Institute Inc., United States) using stratified block randomization with a block length of 10 and stratified by site. A randomized envelope is made by a statistician in our clinical research center. The sequence number is marked outside the envelope and the medication puzzled for vitamin C or NS is sealed inside. The randomization information is blinded to all the participants in the trials except the unblinding drug preparing nurse (UDPN).

After consent is obtained and the inclusion/exclusion criteria are verified, the principal investigator (PI) in each participating site (PS) hands the unique randomized envelope of the participant to UDPN. The UDPN unseals the envelope and disposes the vitamin C or NS into an opaque 50 ml syringe according to grouping information inside the envelope. UDPN gives the opaque syringe to the therapy nurse and is independent of the following medical process. The outcome assessor and statistician are blinded to randomization and are not involved in treatment procedures.

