### Statistical analysis

Categorical data will be described with frequency or ratio. Continuous variables will be described using mean and SD for normally distributed variables or median and interquartile range (IQR) for non-normally distributed variables. Categorical variables will be compared using the chi-square test or the Fisher exact test. Continuous variables will be compared using the t-test for normally distributed variables or the Wilcoxon rank-sum test for non-normally distributed variables. The efficacy analysis will be based on the intention-to-treat principle and compared with the per-protocol principle subset.

The primary outcome of 28 days mortality will be compared between groups using the chi-square test or the Fisher exact test. Superiority could be calculated if the upper bound of 28 days of mortality was lower than the 2.5% superiority margin. Logistic analysis with a 95% CI is used to calculate the odds ratio of each risk factor.

The secondary outcomes of the SOFA score change and inflammatory indicators change on days 1, 3, 7, 14, and day 28 between two groups will be analyzed using a generalized linear model. The incidence of organ failure and adverse events occurrence will be compared using the chi-square tests or the Wilcoxon rank-sum test. The duration of organ support and vitamin C concentration on days 0, 3, 4, and day 7 will be compared using the *t*-test or the Wilcoxon rank-sum test. All these analyses are performed two-sided at the 5% significance level. SAS v. 9.2 (SAS Institute Inc., United States) is used for the analysis.

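### The stated sample size inputs do not give 620: at one-sided 2.5% and zero margin, 620 randomised gives about 70% to 74% power, not 80%

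*Protocol article*

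**What the plan says.** The Sample size section of the protocol article bases the calculation on 28-day mortality, which it puts at 40%. The method is given as "We used the superiority test for two proportions based on the one-sided 2.5% of type I error probability and 80% of power". The result is "A total of 620 participants are required to detect a decrease of 10% mortality rate and 10% dropout rate", and the software named is PASS 15. The section does not say whether the 10% decrease is absolute or relative, and it mentions no margin.

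Allocation is equal: "Participants are randomly assigned to the vitamin C or normal saline (NS) groups in a 1:1 ratio". For the analysis, the Statistical analysis section says "The primary outcome of 28 days mortality will be compared between groups using the chi-square test or the Fisher exact test". It then adds a rule that superiority is shown if an upper bound lies below a superiority margin of 2.5%. The last paragraph of that section, which deals with the secondary outcomes, says "All these analyses are performed two-sided at the 5% significance level". The efficacy analysis follows intention-to-treat, and the Data collection section provides for multiple imputation of missing data.

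**The concern.** The Sample size section gives every input needed to check its own total, and the total is too small for them. The gap is about 170 randomised patients (787 − 620 = 167; 792 − 620 = 172), which is beyond rounding or choice of formula. Even with no allowance for dropout, the evaluable number required (708 to 712) exceeds 620 by about 90.

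This matters because the Introduction and Discussion justify the trial by the small size of two previous trials (167 and 124 patients). If the power at the stated error level is 70% to 74%, the chance of missing the planned 10-point benefit is 26% to 30% rather than 20%. A null result reported beside an 80% figure would look like stronger evidence against that benefit than it is.

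**Working it through.** **Inputs.** Control mortality p1 = 0.40; reduction of 10 points, so p2 = 0.30; one-sided α = 0.025 (z = 1.960); power 80% (z = 0.8416); dropout 10%. All are from the Sample size section. Allocation is 1:1, from the section on randomisation. The absolute reading of the 10% decrease is an assumption, tested in step 3.

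**1. The plan's own inputs.**

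Unpooled: n per arm = (z_α + z_β)² × [p1(1 − p1) + p2(1 − p2)] / (p1 − p2)²
= (1.960 + 0.8416)² × (0.24 + 0.21) / 0.01 = 7.849 × 45 = 353.2, so 354 per arm, 708 evaluable, and 708/0.9 = 787 randomised.

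Pooled (mean proportion 0.35): n = [1.960 × √(2 × 0.35 × 0.65) + 0.8416 × √0.45]² / 0.01 = 355.9, so 356 per arm, 712 evaluable, and 712/0.9 = 792 randomised.

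The stated 620 is not reproduced.

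**2. Other formulas with the same inputs.** Arcsine gives 712 evaluable and 792 randomised. Continuity correction gives 752 and 836. Inflating by N × 1.1 instead of N/0.9 gives 784 (pooled). None is near 620.

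**3. Other readings of the effect.**

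| Reading, one-sided 2.5%, 80% power | Randomised |
|---|---|
| Relative 10% reduction (40% to 36%) | 5,136 |
| 50% vs 40% | 863 |
| 40% vs 30%, superiority margin of 2.5 points | 1,396 |
| 40% vs 30%, margin of 2.5 points in the other direction | 505 |

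None gives 620.

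**4. What does give about 620.**

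| α (one-sided), power | Unpooled | Pooled |
|---|---|---|
| 5%, 80% | 278.2, so 279 per arm, 558, 558/0.9 = 620 | 281 per arm, 562, 625 |
| 2.5%, 70% | 277.7, so 278 per arm, 556, 618 | 281 per arm, 562, 625 |

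One-sided 5% with unpooled variance matches exactly. One-sided 2.5% with 70% power is within two patients unpooled and identical to it when pooled.

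**5. Power of 620 at one-sided 2.5%, zero margin.** Unpooled: power = Φ(0.10 / √(0.45/n) − 1.960).

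- 558 evaluable (n = 279): standard error √(0.45/279) = 0.04016; 0.10/0.04016 − 1.960 = 0.530; power 70.2%. Pooled 69.8%; exact enumeration of the chi-square test 69.9%; Fisher 66.6%.
- All 620 analysed (n = 310): standard error √(0.45/310) = 0.03810; 0.10/0.03810 − 1.960 = 0.665; power 74.7%. Pooled 74.3%; exact chi-square 74.3%; Fisher 71.5%.

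**6. Effect detectable with 80% power at one-sided 2.5%.** With 279 per arm: 40% vs 28.8%, about 11.2 points. With 310 per arm: 40% vs 29.3%, about 10.7 points.

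**7. If the 2.5% were a true margin of 2.5 points.** Replace 0.10 by 0.10 − 0.025 = 0.075. With 279 per arm: 0.075/0.04016 − 1.960 = −0.09, power about 46%. With 310 per arm: 0.075/0.03810 − 1.960 = 0.01, power about 50%.

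**The case against.** The mismatch itself is hard to dispute, since no standard variant of the stated inputs reaches 620. The objections concern how much can be built on it.

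- **Cause.** A reader might infer from the exact match that the calculation was run at one-sided 5%. The article does not show the software output and mentions no one-sided 5% level. The exact match also depends on unpooled variance and division by 0.9, and a mis-stated power of 70% explains the total almost as well. This objection stands: the cause is an inference.
- **A flat 70%.** Intention-to-treat and imputation keep patients in the analysis, and the article does not say that 10% will lack a 28-day vital status. Imputation does not restore lost information, so 70% remains a fair lower figure for the chi-square test, but a range with its conditions is the right statement. This stands in part.
- **Error level of the primary test.** The two-sided 5% sentence closes the paragraph on secondary outcomes, so its reach to the primary comparison is a reading. Little depends on it, because "one-sided 2.5% of type I error probability and 80% of power" is the stated design level, and two-sided 5% corresponds to one-sided 2.5% for superiority.
- **Margin.** The 70% to 74% holds only for a zero margin, and the Statistical analysis section names a margin of 2.5%. A reader might conclude that power is really 46% to 50%. The article does not support that as a finding: the sample size section has no margin, and the sentence in the analysis section bounds mortality itself rather than a difference. The conflict must still be resolved, and a true superiority margin would lower the power further.

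**Conclusion.** Wrong as written. The stated error level, power, mortality rates, dropout and total cannot all be true together. At one-sided 2.5% (two-sided 5%), 40% vs 30% and zero margin, 620 randomised gives about 70% power with 558 evaluable and 74% to 75% with all 620 analysed, a few points less with Fisher's exact test. Reaching 80% would take about 787 to 792 randomised.

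The conclusion assumes an absolute 10-point reduction from 40%; the relative reading makes the mismatch far larger. It does not depend on how 620 was produced. Type I error is not affected. What is wrong is the power claimed for the only primary outcome, and so how a null result would be read.

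**What to change.** Retrieve the PASS output and establish which inputs were used. Then correct the Sample size section to say:

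- for an absolute difference of 40% vs 30% at one-sided 2.5%, 620 randomised gives about 70% power with 558 evaluable and about 74% with 620 evaluable;
- 80% power is reached only for an absolute reduction of about 11.2 points (558 evaluable) or 10.7 points (620 evaluable);
- the 10% decrease is absolute, and these figures assume a zero margin.

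Reconcile the last point with the 2.5% superiority margin in the Statistical analysis section. If a true margin of 2.5 points is intended, the power to state is about 46% to 50%. Do not carry the 80% figure into the report.

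The cost is a less favourable stated power. The correction needs no extra patients and no change of test. Whether to keep 620 is a separate decision for the sponsor.

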### Data collection

All data are collected using a web-based database in each participating center (Table 1). When participants are withdrawn from the study, they are not replaced. Patients that are lost during the study period will be incorporated into the analysis until their final lost date. Missing data are replaced by chained equations using multiple imputations if these missing data are judged to be random.

**TABLE 1 T1:** Collected data and outcomes.

Procedures	Day 0	Day 1	Day 3	Day 4	Day 7	Day 14	Day 28
Eligibility criteria	X						
Informed consent	X						
Demographic and medical data	X						
Vital signs							
Fluid balance							
Routine laboratory test*							
Inflammatory indicators #	X	X	X	X	X	X	X
Plasma vitamin C concentration	X		X	X	X		
SOFA score	X	X	X	X	X	X	X
APACHEII score	X						
Organs support							
Vasoactive drugs							
Adverse events							
Death							X
Hospital stay							X

*Routine laboratory tests include the following: white blood cell (WBC) count, hemoglobin, thrombocytes, blood gas analysis, electrolytes, urea, creatinine, aspartate transaminase, alanine transaminase, lactate dehydrogenase, alkaline phosphatase, NT-proBNP, TnI, and coagulation test. #Inflammatory indicators include the following: C-reactive protein (CRP) and procalcitonin (PCT). SOFA, Sequential Organ Failure Assessment; APACHEII, Acute Physiology And Chronic Health Evaluation II.

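### The rule that keeps lost patients in the analysis up to the date of loss cannot be applied to the chi-square test on 28-day death, and is not reconciled with the conditional imputation rule that follows it

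*Protocol article*

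**What the plan says.** All references are to the protocol article.

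- **Data collection, on lost patients:** "Patients that are lost during the study period will be incorporated into the analysis until their final lost date".
- **Data collection, the sentence that follows:** "Missing data are replaced by chained equations using multiple imputations if these missing data are judged to be random".
- **Data collection, on withdrawals:** "When participants are withdrawn from the study, they are not replaced".
- **Statistical analysis, on the primary outcome:** "The primary outcome of 28 days mortality will be compared between groups using the chi-square test or the Fisher exact test".
- **Statistical analysis, on the analysis set:** "The efficacy analysis will be based on the intention-to-treat principle and compared with the per-protocol principle subset".

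No time-to-event method is named anywhere in the article. The Sample size section allows for 10% dropout in a total of 620. The article does not say how the lost-date sentence and the imputation sentence combine for a patient whose day-28 status is unknown, or what is done if the missingness is not judged random.

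**The concern.** Including a patient up to the date of loss makes sense where the analysis uses time at risk. A test on dead or alive at day 28 does not. A patient last seen alive on day 8 has no cell in the two-by-two table unless someone assigns a status.

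Imputation would assign one, but here it depends on a judgement. Observed data can contradict missingness that is completely at random. They cannot separate missing at random from missing not at random. The article gives no criterion and no time for the judgement, so the handling of the primary outcome could be settled after the data have been seen. If the answer is that the missingness is not random, imputation falls away and only the lost-date rule remains.

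The possible routes (imputing, coding as alive, leaving out) can give different primary results from the same data. Coding as alive understates mortality, and understates it more in the arm with more loss. Leaving patients out departs from the intention-to-treat principle that the article adopts.

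**Working it through.** **1. Can the stated rules be carried out on the primary outcome?**

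| Situation for a patient with unknown day-28 status | Rule that the article supplies | Usable in a chi-square or Fisher test? |
|---|---|---|
| Missingness judged random | Lost-date rule and multiple imputation, order of precedence not stated | Yes, if imputation governs |
| Missingness not judged random | Lost-date rule only | Only by coding the patient as alive or leaving the patient out |

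**2. Inputs for an illustration of size**

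- From the article: 620 patients randomised 1:1, so 620 / 2 = 310 per arm; 28-day mortality 40%; target decrease 10 points (40% against 30%); one-sided 2.5% type I error.
- Assumed, not in the article: the share of each arm with unknown day-28 status, the mortality among those patients, and that none of their deaths is recorded.

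The article gives no figure for loss of vital status, so there is none to reproduce. Its total of 620 enters only as the planned size. That total does not follow from its stated inputs: 356 per arm before dropout, 356 / 0.9 = 396 after, 792 in all. This is a separate matter and does not bear on the present point.

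**3. Formulas**

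Survivor coding: observed rate = true rate − (share lost × mortality among the lost).

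Leaving out: observed rate = (true rate − share lost × mortality among the lost) / (1 − share lost), with n reduced to match.

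With observed rates p1 (control) and p2 (vitamin C), d = p1 − p2, p̄ their mean and n per arm:

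- SE0 = √(2p̄(1−p̄)/n)
- SE1 = √((p1(1−p1) + p2(1−p2))/n)
- chance of finding a benefit = 1 − Φ((1.96·SE0 − d)/SE1)

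**4. Equal true mortality of 40%, survivor coding, 8% lost in control and 12% in vitamin C, 40% mortality among the lost**

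- p1 = 0.40 − 0.08 × 0.40 = 0.368; p2 = 0.40 − 0.12 × 0.40 = 0.352; d = 0.016; p̄ = 0.36
- SE0 = √(2 × 0.36 × 0.64 / 310) = 0.03856; SE1 = 0.03855
- (1.96 × 0.03856 − 0.016) / 0.03855 = 1.545
- chance of a false benefit = 1 − Φ(1.545) = 6.1%, against 2.5%

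**5. Other assumed cases, no true difference (40% in both arms)**

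| Handling | Lost, control / vitamin C | Mortality among the lost, control / vitamin C | Observed rates | False benefit |
|---|---|---|---|---|
| Survivor coding | 10% / 10% | 40% / 40% | 36.0% / 36.0% | 2.5% |
| Survivor coding | 8% / 12% | 40% / 40% | 36.8% / 35.2% | 6.1% |
| Survivor coding | 5% / 15% | 40% / 40% | 38.0% / 34.0% | 17.8% |
| Leaving out (279 per arm) | 10% / 10% | 40% / 40% | 40.0% / 40.0% | 2.5% |
| Leaving out (279 per arm) | 10% / 10% | 30% / 50% | 41.1% / 38.9% | 7.7% |

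**6. Power with a true 40% against 30%**

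Full data on 310 per arm give 74.3%. With 10% lost in each arm and mortality among the lost equal to that of their arm, survivor coding shrinks the rates to 0.9 × 40% = 36% and 0.9 × 30% = 27%, a 9-point difference, with power 67.5%. Leaving the lost out gives 69.8%.

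**The case against.** A reader might infer that lost patients will be either counted as survivors or dropped. The article does not support that. It never states either coding, and the imputation sentence offers a third route that keeps every randomised patient in the chi-square comparison, in line with "The efficacy analysis will be based on the intention-to-treat principle". The two crude options arise only if the missingness is not judged random, or if the lost-date rule overrides imputation. The text settles neither.

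The lost-date sentence also names no outcome. It may be meant for the repeated measurements (SOFA, C-reactive protein, procalcitonin), where using what was observed before loss is natural. On that reading the two sentences complement each other. This is plausible, and it is why the fix keeps a place for the sentence. But as written it covers the analysis in general, the primary outcome included.

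The 10% dropout allowance is not stated to be the rate of unknown vital status. Death at day 28 is on the data collection schedule, and nothing says that stopping the study drug ends follow-up, so the true rate may be well below 10%. The imbalances and the mortality among the lost are likewise assumed. This stands, and the figures are illustrations for that reason.

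Chained-equations imputation in its usual form itself assumes missing at random, so attaching that condition is not an error in principle. This is fair. The difficulty is that the condition is made a switch, with no usable rule on the other side. The article says the statistician is blinded to randomisation, which would limit the harm if the judgement were made blind, but it does not say that it will be.

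Finally, imputation models and sensitivity analyses are commonly left to a statistical analysis plan, which may exist. Their absence is not the point. The point is two stated rules that do not fit together or, in one case, the primary test.

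**Conclusion.** The concern holds as a defect in stated rules. The lost-date rule cannot be used by the primary test, it is not reconciled with imputation, and imputation is conditional on a judgement that the data cannot verify and that may be made after they are seen. How a lost patient's day-28 status enters the intention-to-treat comparison is therefore open.

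The size is conditional. Under the assumptions of 40% mortality in both arms and among the lost, survivor coding, and unknown status in 8% against 12%, the chance of a false benefit is about 6% instead of 2.5%. Wider imbalance raises it. Equal, non-informative loss leaves it at 2.5%, and at 10% loss the choice between survivor coding and leaving out then moves power by only about 2 points (67.5% against 69.8%). That the choice could change the trial's conclusion is a possibility that depends on differential or informative loss, not a prediction. The point should be corrected before analysis.

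**What to change.** For the primary outcome, state one rule fixed in advance:

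1. Use day-28 vital status for every randomised patient for whom it is known, including those who stopped study treatment.
2. Multiply impute any day-28 status still missing, by arm, in the primary intention-to-treat analysis. Remove the condition that missingness be judged random, and state missing at random as the working assumption. Use site (the stratification factor) and the SOFA and APACHE II scores, which Table 1 already schedules.
3. Add a tipping-point sensitivity analysis that shows how far mortality among the missing would have to depart from the imputed values, by arm, to change the conclusion.
4. Limit the lost-date sentence to the repeated measures, or to a Kaplan-Meier sensitivity analysis of 28-day mortality.

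The cost is a change of wording in the protocol or analysis plan, a vital-status check for the lost patients, and slightly more analysis work. No new measurements are needed.

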### Statistical analysis

Categorical data will be described with frequency or ratio. Continuous variables will be described using mean and SD for normally distributed variables or median and interquartile range (IQR) for non-normally distributed variables. Categorical variables will be compared using the chi-square test or the Fisher exact test. Continuous variables will be compared using the t-test for normally distributed variables or the Wilcoxon rank-sum test for non-normally distributed variables. The efficacy analysis will be based on the intention-to-treat principle and compared with the per-protocol principle subset.

The primary outcome of 28 days mortality will be compared between groups using the chi-square test or the Fisher exact test. Superiority could be calculated if the upper bound of 28 days of mortality was lower than the 2.5% superiority margin. Logistic analysis with a 95% CI is used to calculate the odds ratio of each risk factor.

The secondary outcomes of the SOFA score change and inflammatory indicators change on days 1, 3, 7, 14, and day 28 between two groups will be analyzed using a generalized linear model. The incidence of organ failure and adverse events occurrence will be compared using the chi-square tests or the Wilcoxon rank-sum test. The duration of organ support and vitamin C concentration on days 0, 3, 4, and day 7 will be compared using the *t*-test or the Wilcoxon rank-sum test. All these analyses are performed two-sided at the 5% significance level. SAS v. 9.2 (SAS Institute Inc., United States) is used for the analysis.

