**Methods and design:**

Here, we are conducting a prospective, multi-centered, double-blinded, randomized, and placebo-controlled superiority study named High-Dose Vitamin C on Sepsis (HDVCOS). A total of 620 participants diagnosed with sepsis in four participating sites across China that satisfy the eligibility criteria will be randomized at a ratio of 1:1 to receive treatment with a high-dose intravenous injection of vitamin C (200 mg/kg/24 h) or placebo (saline) for 4 days. The primary outcome is 28 days of mortality. The secondary outcomes include the incidence of organ failure, Sequential Organ Failure Assessment (SOFA) score change, organ support, the relationship between plasma vitamin C concentration and outcomes, and adverse events.

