## Methods and analysis

### Study design

We have designed the High-Dose Vitamin C on Sepsis (HDVCOS) study as a prospective, multi-centered, double-blinded, randomized, placebo-controlled, superior clinical trial. Till now, five centers in China have been involved. The trial protocol is approved by the Clinical Trail Ethics Committee of Ruijin Hospital of Shanghai Jiao Tong University School of Medicine (2018-145) and all the participating centers. This trial has been registered in the Chinese Clinical Trial Registry (ChiCTR1800017633). A total of 620 participants diagnosed with sepsis that satisfy the eligibility criteria will be randomized at a ratio of 1:1 to receive treatment with a high-dose intravenous injection of vitamin C (200 mg/kg/24 h) or placebo (saline) for 4 days.

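### The primary chi-square test uses neither the site strata nor the Day-0 severity scores, and gives up several points of power that are cheap to recover

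*Protocol article*

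**What the plan says.** - Primary test (Statistical analysis): "The primary outcome of 28 days mortality will be compared between groups using the chi-square test or the Fisher exact test". No stratification factor or covariate is attached to it.
- Design (Randomization, Blinding, and allocation): the sequence is generated by "stratified block randomization with a block length of 10 and stratified by site".
- Number of sites: the abstract counts four. The Study design section says "Till now, five centers in China have been involved".
- Baseline severity (Data collection, Table 1): the row "APACHEII score" is marked on Day 0 only. The SOFA row is marked on Day 0 and at every later visit.
- The only regression model named for mortality (Statistical analysis): "Logistic analysis with a 95% CI is used to calculate the odds ratio of each risk factor". It lists no covariates and is not tied to the comparison of arms.

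**The concern.** An analysis should follow the randomisation. If mortality differs between sites and allocation is balanced within them, a test that ignores site uses a standard error that is too large and is slightly conservative.

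The larger matter is severity. Patients enter from a SOFA score of 2 upwards, so baseline risk can vary widely. Randomisation is not stratified on it, and the primary test ignores it. A prognostic baseline covariate in the primary model removes explained variation from the treatment comparison and corrects for whatever imbalance chance produces. The scores are already scheduled, so no new data are needed.

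The stake is power. The stated sample size does not deliver 80% at the stated significance level (shown in the working), so precision lost in the analysis matters more here than in a trial with power to spare.

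**Working it through.** **Inputs from the protocol.** Control mortality 40%; a decrease of 10%, read as 40% versus 30% absolute; one-sided 2.5% level; 80% power; 10% dropout; N = 620; 1:1 allocation (Sample size; Randomization).

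**Assumed, because the protocol gives no figure.** The AUC of the severity score for 28-day death, 0.60 to 0.79; the between-site SD of mortality on the logit scale, 0 to 0.5, with 0.8 as a wider case; five sites.

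**1. The plan's sample size.** With p1 = 0.40, p2 = 0.30 and mean 0.35:

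n per arm = [z_α √(2 × 0.35 × 0.65) + z_β √(0.24 + 0.21)]² / 0.10²

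= [1.960 × 0.6745 + 0.8416 × 0.6708]² / 0.01 = 356

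That is 712 in total, and 712 / 0.9 = 791.1, or 792 with equal arms. The stated 620 does not reproduce. It does at one-sided 5% with unpooled variance: (1.6449 + 0.8416)² × 0.45 / 0.01 = 278.2, so 279 per arm, 558 in total, and 558 / 0.9 = 620.

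**2. Power of the unadjusted test at one-sided 2.5%.** Power = Φ{[0.10 √n − 1.960 × 0.6745] / 0.6708}.

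- 558 evaluable (n = 279 per arm): Φ(0.519) = 69.8%.
- All 620 (n = 310 per arm): Φ(0.654) = 74.3%.

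**3. Power with adjustment.** Trials were simulated from logit P(death) = a + d·arm + b·score + site effect. The score was standard normal, a and d were set so that marginal mortality is 40% versus 30%, and allocation was balanced within five sites. Each test was run at two-sided 5%, counting rejections in the direction of benefit. The adjusted analysis was a logistic model with arm, score and site. In this table the site effects were zero, so the gain comes from the score alone. There were 4,000 trials per row; the Monte Carlo standard error of each power is about √(0.7 × 0.3 / 4,000) = 0.7 points.

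| Score AUC | 558: chi-square | 558: adjusted | Gain (points) | 620: chi-square | 620: adjusted | Gain (points) |
|---|---|---|---|---|---|---|
| 0.60 | 68.9% | 69.8% | 0.9 | 73.6% | 74.7% | 1.1 |
| 0.65 | 69.9% | 72.9% | 3.0 | 73.7% | 76.5% | 2.8 |
| 0.69 | 69.7% | 74.1% | 4.4 | 74.3% | 79.1% | 4.8 |
| 0.74 | 70.2% | 78.2% | 8.1 | 73.6% | 82.2% | 8.6 |
| 0.79 | 70.3% | 80.9% | 10.6 | 75.0% | 86.2% | 11.1 |

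Gains are computed before rounding. The standardised (marginal) risk difference from the same model had power within 0.1 points of the adjusted column in every row. The gain therefore does not require giving up the marginal estimand of the chi-square test.

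**4. Site and severity together.** With site SD 0.4, 558 evaluable, blocks of 10 and 1,500 trials per setting (standard error about 1.1 points):

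| Score AUC | Chi-square | Cochran-Mantel-Haenszel by site | Site + severity |
|---|---|---|---|
| 0.67 | 69.6% | 70.4% | 73.3% |
| 0.73 | 71.5% | 72.3% | 79.2% |
| 0.77 | 70.2% | 70.7% | 78.5% |

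The gains from site plus severity are 3.7, 7.7 and 8.3 points. Stratifying by site alone adds less than 1 point.

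**5. Site alone at other spreads.** With 558 evaluable and no severity effect, chi-square versus Cochran-Mantel-Haenszel was 69.5% versus 69.4% at SD 0, 72.5% versus 72.8% at SD 0.3, and 70.8% versus 72.2% at SD 0.5. At 620 and SD 0.5 it was 76.2% versus 78.1%. At an assumed SD of 0.8, a logistic model with site added about 3 points.

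**6. Type I error.** With no treatment effect (6,000 trials, 558 patients, AUC about 0.70), the one-sided rejection rate was 2.4% for chi-square, for the adjusted logistic model and for the standardised risk difference.

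**The case against.** The strongest reply is that nothing here is invalid. A crude comparison of two proportions is a legitimate analysis of a randomised binary outcome and matches the test used for sizing. Its error rate already allows for chance imbalance. Ignoring site costs little, so a site-stratified test on its own would recover almost none of the loss. The severity gain rests on an AUC that the protocol does not give, and near 0.60 it is only 1 to 2 points. The shortfall from 80% is a sample-size problem, and adjustment is not its remedy. Adjusted models are also often left to the SAP, which is not shown.

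Much of this stands: the loss is efficiency and not bias, nearly all of it comes from severity, its size is conditional, and unadjusted power is about 74% rather than 70% if all 620 are analysed. The change also needs a rule for missing baseline scores and a variance method for the risk difference, so its cost is small but not zero. The simulations test against no difference and do not apply the 2.5% superiority margin mentioned in the same section; applying it would change the power of every test compared here.

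The SAP argument does not stand. The article is not silent on the primary test: it names one, and the one it names is unadjusted. A logistic analysis of unspecified risk factors does not make the primary comparison an adjusted one.

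**Conclusion.** The point holds. The stated primary test ignores the stratification factor and the Day-0 severity scores. At 40% versus 30% with 558 evaluable patients, adjusting for site and severity raises power from about 70% by roughly 4 to 8 points if the score's AUC is 0.67 to 0.77. Over AUCs of 0.60 to 0.79 the range is 1 to 11 points, and the gain is similar with all 620 analysed. Site alone contributes 0 to 2 points for a logit SD up to 0.5. Type I error is unaffected.

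These sizes rest on assumed AUCs and site spreads; the direction does not. The change should be made, but the trial remains valid without it. Adjustment recovers most or all of the shortfall from 80% only if the score is strongly prognostic.

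**What to change.** - Make the primary analysis a logistic model for 28-day death with arm, site and one named Day-0 severity score (APACHE II or SOFA) as a continuous term. Report the standardised risk difference with 95% CI, and the odds ratio.
- State the variance method for the risk difference, the rule for a missing Day-0 score, and that only values recorded before the first infusion count.
- If the sponsor prefers a simple test, use at least a Cochran-Mantel-Haenszel test stratified by site. This follows the design but recovers little power.
- Keep the crude chi-square test as a supportive result.
- Separate this treatment model from the risk-factor logistic analysis.

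The cost is SAP wording and a few lines of code; the data are already scheduled. The Monitoring section says data are analysed at study completion, so the change can be fixed before unblinding. The mismatch between 620 patients and the one-sided 2.5% level still has to be dealt with separately.
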